### Participants

Children from Malletts Bay School in grades 3rd, 4th, and 5th grade and ranging in age from 7 to 11 years will be recruited. An IRB approved consent form, group information form, as well as an introduction to the study letter will be sent home with each student. The letter will provide instructions as to how each interested student (along with a parent/legal guardian signature) should complete the consent form and group information form. Students will return their signed consent form along with a completed group information form to their teacher. Study staff will collect and review completed consent forms from the teachers.

Children will indicate on the group information form (included with the consent form) the group (A or B) they would like to participate (Table 1). The investigators will randomize the children to either Group A or Group B on a first-come, first-served basis. Once the maximum capacity for any one group (n = 50) is reached, children will be randomized to the other group if they have indicated their willingness to participate in the other group. Or if the preferred group is at maximum capacity and the child did not request to participate in the other group, then the child would be notified in writing that the requested group was no longer available.

**Table 1 T1:** Group Stratification

**Group A**	Week 0	Physical Activity Program	Week 12
	tests and measures	3 days/week	tests and measures
**Group B**	Week 0	No Physical Activity Program	Week 12
	tests and measures		tests and measures

Once the consent form is received by the study staff, children and parents will be notified through letters mailed to their home address as to what group their child will be participating. The parent(s) of the child will then be contacted by phone to schedule the first testing session.

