### Assessments

All participant baseline measures will be performed 1–2 weeks prior to the first physical activity session. Follow-up measures will be performed within 1 week following the final physical activity session. For both Group A and Group B, the testing and measurement sessions will be scheduled at a convenient time before or after school and will be performed in a private room at the school. At the two testing and measurement visits, study staff will obtain weight, height, waist, hip and neck circumferences, resting heart rate and blood pressure for each enrolled child. Children will be asked to complete several questionnaires at both baseline and follow-up regarding their physical activity, eating habits, feelings and emotions, and quality of life. These measurements and questionnaires are expected to take approximately 15–20 minutes. Parent(s) will also be asked to complete questionnaires before and after the physical activity program. The parent questionnaires will include information regarding their education level, their child’s physical activity, eating habits, medications, illnesses, family history and quality of life. These questionnaires will be directly mailed to the parents and will include a postage-paid return envelope. We will also be asking teachers of enrolled participants to complete a brief questionnaire regarding the child’s classroom behavior before and after the physical activity program.

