#### Data analysis

All statistical procedures will be performed in SPSS, version 18.0. Significance will be set at the 0.05 level. Descriptive statistics including means and standard deviations will be computed for all of the data. Differences among the groups at Week 0 and Week 12 will be assessed by using Student’s independent *t*-test. Furthermore to account for baseline differences, a general linear mixed-model analysis of variance will be performed. A power analysis was performed to determine the sample size needed to determine significant pre- and post-differences in each group. With the alpha level set at 0.05, an anticipated effect size of 0.8, and the statistical power level set at 0.8, the minimum total required sample size was 8 participants. A power analysis was performed to determine the sample size needed to determine significant differences between Group A and Group B with a one-tailed *t*-test. With the alpha level set at 0.05, an anticipated effect size of 0.8, and the statistical power level set at 0.8, the minimum total required sample size was 42, with a minimum sample size per group of 21 participants. Therefore, with the planned total of 100 participants in this study, 50 of which will be assigned to Group A and 50 assigned to Group B, the minimum sample size required for analyses will be achieved.

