## Discussion

The proposed study described in this paper is the first to the authors’ knowledge to examine the effect of an unstructured, moderate to vigorous, before-school physical activity program on academic performance, classroom behavior, emotions, and other health related measures in elementary school-aged children. The results of this study will provide evidence to support the feasibility and efficacy of an unstructured, moderate to vigorous, before-school physical activity program in children. The unstructured physical activity with limited equipment, yet moderate to vigorous intensity design would allow others to easily and affordably replicate. Often, the initiation of novel physical activity programs is often viewed as cost-prohibitive and labor intensive. The design, setting, and population, however, may be replicated in relatively any elementary school with limited supplies and with a limited budget. Furthermore, the proposed study will provide insight regarding the ideal physical activity intensity and duration necessary to achieve a positive increase in academic performance.

The current study allows the participants to select and/or indicate their preferred group- Group A, tests and measures with the physical activity intervention or Group B, tests and measures only. This randomization design may be considered a limitation of the study; however, differences within each group, treatment and control will be assessed in addition to comparisons between the two groups. These within-group analyses will allow evaluation of the outcomes attributable to the physical activity intervention rather than attitudinal variables that may have been introduced with the self-selection of the groups.

The findings of this study will provide valuable information for other research groups looking to increase physical activity levels of children via school-based interventions. Furthermore, it will ascertain whether an unstructured, moderate to vigorous, before-school physical activity program is an effective method for future large-scale implementation.

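### The stated analyses of the self-chosen groups do not remove differences in 12-week change that come from measured characteristics, and no use of the planned parent data is named

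*Protocol article*

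**What the plan says.** **Group formation.** Under Participants, each family names a group on the information form. The text then says "The investigators will randomize the children to either Group A or Group B on a first-come, first-served basis", with 50 places per group. The Discussion is open about this: "The current study allows the participants to select and/or indicate their preferred group".

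**Between-group analysis.** Under Data analysis, "Differences among the groups at Week 0 and Week 12 will be assessed by using Student’s independent" t-tests. The next sentence is the only adjusted analysis: "Furthermore to account for baseline differences, a general linear mixed-model analysis of variance will be performed". No model terms are listed.

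**Other handling of self-selection.** The Discussion says: "These within-group analyses will allow evaluation of the outcomes attributable to the physical activity intervention rather than attitudinal variables" introduced by self-selection.

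**Planned parent data.** Under Assessments: "The parent questionnaires will include information regarding their education level, their child’s physical activity, eating habits, medications, illnesses, family history and quality of life". Parents are asked before and after the program, by mail with a return envelope. Data analysis gives these variables no role beyond descriptive statistics computed for all data.

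**The concern.** With two time points, a group-by-time model subtracts each group's starting level and compares the changes. That deals with a stable difference at Week 0. It does not deal with groups that would have changed at different rates without the program, because that difference goes into the interaction and reads as a program effect.

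The article itself gives reasons to expect imbalance:
- Families choose the group.
- First-come filling favors families who return forms quickly.
- A doctor's written approval is required for Group A only, which can sort children by illness and medication.
- About 35% of the school's students are in the Free and Reduced Lunch Program, so household circumstances vary.

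Parent education, illness and medication could plausibly relate both to joining and to 12-week gain in reading, mathematics, behavior or mood. The Discussion expects the results to support claims of efficacy and to inform large-scale implementation. The between-group comparison has to carry that inference.

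**Working it through.** **The plan's own figure.** The between-group sample size (one-tailed t-test, alpha 0.05, effect size 0.8, power 0.8) reproduces: the noncentral t gives 21 per group with power 0.817. It is not in dispute, and this point changes no sample size.

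**What the model estimates.** The interaction is (A at Week 12 − A at Week 0) − (B at Week 12 − B at Week 0). With two time points this equals a two-sample t-test on the changes. Write a child's change as α + τ·group + β·U + error, where U is a baseline characteristic. The expected interaction is then τ + β·(mean U in A − mean U in B). The second term is bias. In SD of change:

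bias = Δ × r

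Here Δ is the standardised group difference in U, and r is its correlation with change.

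**Inputs.** From the article: 50 per group and alpha 0.05. Assumed, because the article gives no values: Δ from 0.2 to 0.5 and r from 0.1 to 0.3. As a guide to Δ, 60% against 40% with higher parent education is 0.20/√(0.5 × 0.5 − 0.1²) = 0.20/√0.24 = 0.41 SD.

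**False-positive rate when the program has no effect.** This uses the noncentral t with 98 df and noncentrality bias × √(50/2) = 5 × bias. Critical values are 1.984 (two-sided) and 1.661 (one-tailed, the sidedness used for sizing).

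| Δ, r | Bias (SD of change) | Noncentrality | Two-sided | One-tailed |
|---|---|---|---|---|
| none | 0 | 0 | 5.0% | 5.0% |
| 0.2, 0.1 | 0.02 | 0.10 | 5.1% | 6.1% |
| 0.4, 0.2 | 0.08 | 0.40 | 6.8% | 10.6% |
| 0.5, 0.3 | 0.15 | 0.75 | 11.5% | 18.4% |
| three covariates, each 0.3, 0.2 | 3 × 0.06 = 0.18 | 0.90 | 14.5% | 22.6% |

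The last row assumes three mutually independent covariates that all act in the same direction.

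**Does adding the covariate work?** In 20,000 simulated trials per case, the unadjusted two-sided rates for the three single-covariate cases were 5.1%, 6.6% and 11.2%. With the covariate added they were 4.9%, 4.8% and 4.8%. For the three-covariate case the rate was about 14% unadjusted and about 5% adjusted, with no loss of precision.

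**If the sentence instead means adjusting for the Week 0 outcome as a covariate.** A separate simulation used stronger assumptions: Δ of 0.5 to 0.8, a Week 12 shift of 0.3 to 0.5 SD per SD of the confounder, and pre-post correlation 0.7. The change analysis gave false positives in 16% to 57% of trials, and adjustment for the Week 0 outcome gave 16% to 63%. With the confounder included, both were about 5%. The confounder was unrelated to the Week 0 outcome by construction. If the two were related, Week 0 adjustment would absorb part of the bias.

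**The within-group analyses.** A pre/post change in a self-chosen group combines any program effect with maturation, 12 weeks of schooling and motivation. It contains no contrast that separates them, so it is not an adjustment for self-selection.

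**The case against.** The strongest objection is that this argues from silence. Data analysis gives the mixed model one sentence. It does not list terms, does not confine baseline differences to the outcome, and does not say the parent variables are excluded. A covariate list is commonly left to an analysis plan, and that plan is not shown. This stands as a limit: a reader might infer that the plan rules out covariates, and the article does not say so. What survives is that the article does state how self-selection will be handled, by the mixed model and the within-group analyses. On the natural reading the first does not address differing rates of change, and the second is credited with something it cannot do.

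Three further objections are fair:
- A reader might assume the parent data are in hand for every child. They are planned, collected by mail, and may be incomplete.
- The simulated return to about 5% follows from adjusting for the only confounder that was simulated. It shows that the remedy works on measured confounders, and says nothing about attitude or motivation, which is the concern the Discussion raises.
- All confounder sizes are assumed. The middle case reaches only 6.8%, and the 14.5% case needs three covariates pointing the same way.

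The Discussion also concedes that its allocation may be a limitation. That concession does not alter the analysis.

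**Conclusion.** The point holds in a limited form. With groups formed by preference, neither stated analysis removes differences in 12-week change due to measured characteristics that also influence group choice. Data analysis names no use of the baseline data that could reduce them.

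For a single covariate under the assumed ranges, the bias is 0.02 to 0.15 SD of change and the two-sided false-positive rate is about 5.1% to 11.5% instead of 5%. This rests on 50 per group, no true effect, the group-by-time reading of the model, and values of Δ and r that the article does not give. At the low end the effect is negligible.

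Two stronger conclusions may tempt a reader. One is that false-positive rates of 16% to 57% are to be expected. Those figures come from larger assumed confounding, and nothing in the article supports choosing them. The other is that covariate adjustment would make the comparison as good as a randomized one. It would not, because motivation and preference are unmeasured.

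**What to change.** In the Data analysis section:

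1. Name the terms of the mixed model. Add pre-specified baseline covariates that the trial plans to collect or will know: parent education, illnesses and medications as recorded, grade and sex. Include each covariate's interaction with time so that it acts on the change. Equivalently, regress 12-week change on group plus these covariates.
2. Take the group-by-time term (or the group term in the change regression) as the between-group result, and report the result without the added covariates beside it.
3. Keep children whose parent forms are not returned by imputing the baseline covariates.
4. State that adjustment reduces self-selection bias but does not remove it, since motivation is unmeasured.

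In the Discussion, replace the claim for the within-group analyses with a statement that those changes are descriptive and cannot be attributed to the program.

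The cost is wording, a few degrees of freedom out of about 98, and some imputation. No new data collection is needed. If covariates were already intended, naming them settles the modelling part of this point.

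### The stated minimum of 8 participants for pre-post differences does not follow from the printed inputs: a paired t-test needs 12 (one-sided) or 15 (two-sided) per group

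*Protocol article*

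**What the plan says.** The Data analysis section of the protocol article reports two power calculations.

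- **Pre-post.** The aim is to detect "significant pre- and post-differences in each group". The inputs are given as "With the alpha level set at 0.05, an anticipated effect size of 0.8" and power 0.8, and the result is that "the minimum total required sample size was 8 participants". No test, sidedness, type of effect size or pre-post correlation is given for this calculation. The section's only general statement on the significance level is "Significance will be set at the 0.05 level".
- **Between groups.** The aim is to detect "significant differences between Group A and Group B with a one-tailed" t-test. Alpha, effect size and power are the same three values. The result is 42 in total, 21 per group.

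The section then plans 100 children, 50 per group, and concludes that the required minimum will be reached. The Discussion relies on the within-group analyses: because families choose their group, it looks to the change within each group to separate the programme's effect from attitudes linked to self-selection.

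**The concern.** The article prints what looks like a complete set of inputs (alpha, effect size, power) and a result that the usual calculation from them does not give. The simplest test of a pre-post difference within one group is the paired t-test, and 8 is too small for it whichever sidedness is used.

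The wording is also unclear. The aim is expressed for each group, but the answer is a total. In the companion calculation the total covers both groups, with the per-group number given beside it. Here no per-group number appears, so the reader cannot tell what the 8 counts.

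What is at stake is the accuracy of a published figure that supports analyses on which the Discussion relies. The article also presents the design as easy to replicate. Anyone who reused 8 at this effect size with a paired t-test would have well under the stated power.

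**Working it through.** **Inputs, all from the Data analysis section.** Alpha 0.05; effect size 0.8; power 0.80; a pre-post comparison in each group. Sidedness is not stated for this calculation, so both are shown. The effect-size type is not stated; it is first read as the mean change divided by the SD of the change, dz = 0.8 (an assumption).

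**Step 1: reproduce the companion figure.** For an exact one-tailed two-sample t-test, df = 2n − 2 and the noncentrality is 0.8·√(n/2).
- n = 20 per group: noncentrality 0.8·√10 = 2.530, power 0.799.
- n = 21 per group: noncentrality 0.8·√10.5 = 2.592, power 0.817.

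The smallest n reaching 0.80 is 21, as printed. The normal approximation gives 20. So the article's figure matches an exact t-test with 0.8 as a standardised mean difference.

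**Step 2: the pre-post figure by the same approach.** For the exact paired t-test, df = n − 1 and the noncentrality is 0.8·√n. Power is the probability that a noncentral t exceeds the critical value (either tail if two-sided).

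| n | Noncentrality | Power, one-sided | Power, two-sided |
|---|---|---|---|
| 8 | 2.263 | 0.653 | 0.496 |
| 11 | 2.653 | 0.795 | 0.668 |
| 12 | 2.771 | **0.829** | 0.714 |
| 14 | 2.993 | 0.883 | 0.790 |
| 15 | 3.098 | 0.903 | **0.821** |

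The required n is 12 one-sided or 15 two-sided. At n = 8 the shortfall from 0.80 is about 15 points one-sided and 30 points two-sided.

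**Step 3: could a cruder formula give 8?** The normal approximation is n = ((z for alpha + z for power)/0.8)².
- One-sided: 9.66, rounded up to 10.
- Two-sided: 12.26, rounded up to 13.

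Its power at n = 8 is 0.732 and 0.619. Neither version gives 8.

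**Step 4: which unstated inputs would give 8?**
- *0.8 on the raw-score SD scale, with pre-post correlation r.* Then dz = 0.8/√(2(1 − r)). With r = 0.7, dz = 1.033 and the smallest one-sided n is 8 (power 0.836). With r = 0.8, dz = 1.265 and the smallest two-sided n is 8 (power 0.864). The lowest r at which 8 suffices is 0.67 one-sided and 0.76 two-sided.
- *0.8 as ANOVA f, with two groups and two time points, within-subject test.* The noncentrality is f²·N·2/(1 − r), with 1 and N − 2 df. For N = 8 in total, r = 0.10 gives 0.64·8·2/0.90 = 11.38 and power 0.801; r = 0.25 gives 0.64·8·2/0.75 = 13.65 and power 0.866. At r = 0.25, N = 7 gives 0.787.

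Both routes need a correlation that the article does not print. The second also needs 0.8 to mean something different from what it means in the between-group calculation.

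**Step 5: effect on the trial.** With dz = 0.8 and 50 per group, two-sided paired power is above 0.999. At the companion minimum of 21 per group it is 0.936.

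**The case against.** The strongest reply is that the article names neither a paired t-test nor an effect-size type for this calculation, and that the only repeated-measures method it mentions is a mixed-model analysis of variance. On that basis a total of 8 can be obtained from f = 0.8 with a modest assumed correlation, and this reading also explains why the result is a total. This part stands: 8 is not impossible, and it does not depend solely on a high correlation. What does not stand is that 8 follows from what is printed. The same phrase, "an anticipated effect size of 0.8", serves both calculations, and in the second it behaves as a standardised mean difference. An f of 0.8 is a much larger effect.

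A second reply is that sidedness, metric and correlation are details that an article may leave to a fuller document. Their absence alone would not be a finding. The finding is that the printed result disagrees with the natural reading of the printed inputs.

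A third reply, that the trial is unaffected, is correct and sets the severity.

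A reader might be tempted to go further in three ways that the article does not support:
- **Quoting only the two-sided 50%.** Sidedness is not stated here, and the one place where the section states it says one-tailed, so 65% and 50% belong together.
- **Reading the total as 4 children in each group.** The wording allows this but does not establish it.
- **Expecting 8 to be used for subgroup or per-grade analyses.** None is planned, and the within-group analyses concern groups of 50.

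**Conclusion.** The point holds as a minor error in a stated figure. Taken as a paired t-test with a standardised mean change of 0.8 at alpha 0.05, 8 children give 65% power one-sided or 50% two-sided instead of 80%. The correct minimum is 12 or 15 per group, which is 4 or 7 more than printed (50% or 88% more).

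This rests on two assumptions: that the pre-post calculation is a paired t-test, and that 0.8 is the mean change in units of the SD of the change. The match with 21 per group supports an exact t-test and a standardised mean effect. It cannot show which SD was used for the change, so a raw-scale effect with a correlation of about 0.7 (one-sided) or 0.8 (two-sided) remains possible, though unstated.

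The trial is not underpowered for this comparison at the assumed effect. Both corrected figures lie below the 21 per group that the between-group calculation requires and well below the 50 planned, so the article's conclusion about its sample size stands.

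**What to change.** Change one sentence in the Data analysis section, in one of two ways.

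- **Correct the figure.** State that a paired t-test at alpha 0.05, with a standardised mean change of 0.8 and power of 0.80, needs 12 children per group if one-sided or 15 per group if two-sided. Name the sidedness that applies, and give the number per group, not as a total.
- **Keep 8 and justify it.** State the test, the effect-size metric, the sidedness and the assumed pre-post correlation that produce it, and say whether 8 counts one group or both.

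The cost is one sentence. Recruitment, group sizes and planned analyses stay as they are.

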## Discussion

The proposed study described in this paper is the first to the authors’ knowledge to examine the effect of an unstructured, moderate to vigorous, before-school physical activity program on academic performance, classroom behavior, emotions, and other health related measures in elementary school-aged children. The results of this study will provide evidence to support the feasibility and efficacy of an unstructured, moderate to vigorous, before-school physical activity program in children. The unstructured physical activity with limited equipment, yet moderate to vigorous intensity design would allow others to easily and affordably replicate. Often, the initiation of novel physical activity programs is often viewed as cost-prohibitive and labor intensive. The design, setting, and population, however, may be replicated in relatively any elementary school with limited supplies and with a limited budget. Furthermore, the proposed study will provide insight regarding the ideal physical activity intensity and duration necessary to achieve a positive increase in academic performance.

The current study allows the participants to select and/or indicate their preferred group- Group A, tests and measures with the physical activity intervention or Group B, tests and measures only. This randomization design may be considered a limitation of the study; however, differences within each group, treatment and control will be assessed in addition to comparisons between the two groups. These within-group analyses will allow evaluation of the outcomes attributable to the physical activity intervention rather than attitudinal variables that may have been introduced with the self-selection of the groups.

The findings of this study will provide valuable information for other research groups looking to increase physical activity levels of children via school-based interventions. Furthermore, it will ascertain whether an unstructured, moderate to vigorous, before-school physical activity program is an effective method for future large-scale implementation.

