**Discussion:**

The proposed study explores an innovative method of engaging and increasing physical activity in children. The results of this study will provide evidence to support the feasibility of an unstructured, moderate to vigorous, before-school physical activity program in children and provide insight regarding the ideal physical activity intensity and duration necessary to achieve a positive increase in academic performance.

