### Intervention

Group A will participate in a before-school (7:30–8:15 a.m.), physical activity program for 12 weeks, 3 days a week (Tuesday, Wednesday, and Thursday). Children will be able to choose their preferred activity (including but not limited to walking, jogging, running, soccer, jump rope, and basketball). Each child will wear a Polar E600 heart rate monitor (chest strap and watch) during each activity session. We will ask each child to engage in moderate to vigorous physical activity with their heart rate ranging from approximately 120 beats per minute to 180 beats per minute. Each child will be provided a target heart rate based on their age before each session. All activity will be freely chosen by study participants while being encouraged to maintain an acceptable heart rate. Heart rate will be recorded and downloaded following each activity session. Study staff will also check and manually record each child’s heart rate a minimum of three times during each 45 minute session.

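### The article promises insight into the ideal activity intensity and duration, but the design compares one fixed program with none and no stated analysis links exposure to academic outcomes

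*Protocol article*

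**What the plan says.** **The promise.** The closing Discussion says "the proposed study will provide insight regarding the ideal physical activity intensity and duration necessary to achieve a positive increase in academic performance". The Discussion paragraph of the Abstract says that the results will "provide insight regarding the ideal physical activity intensity and duration necessary to achieve a positive increase in academic performance". The Background names ideal duration and intensity as a question needing more research, so the promise answers a gap that the article itself identifies.

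**The design.** Table 1 (Participants) has two groups. Group A has the program on 3 days a week; Group B has "No Physical Activity Program". Under Intervention, all of Group A has the same 45-minute session before school, on the same three weekdays, for 12 weeks. Children are asked for "moderate to vigorous physical activity with their heart rate ranging from approximately 120 beats per minute to 180 beats per minute", and each is given an age-based target before the session. The section adds: "All activity will be freely chosen by study participants while being encouraged to maintain an acceptable heart rate".

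**The exposure data.** "Heart rate will be recorded and downloaded following each activity session", and staff also record it by hand at least three times per session. The PAQ-C questionnaire measures activity in both groups at baseline and follow-up.

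**The analysis.** Data analysis says "Descriptive statistics including means and standard deviations will be computed for all of the data". It then names t-tests between the groups at Weeks 0 and 12 and a mixed-model ANOVA to account for baseline differences. The Discussion adds within-group comparisons. The two power calculations concern pre-post change and Group A versus Group B.

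**The concern.** To say which intensity or duration is ideal for academic gain, a study needs at least two levels of each to compare, or an analysis that relates the amount of activity to the outcome. The design assigns one level against none, and the stated analyses contain no such relation. The Abstract and Discussion therefore announce a dose-response conclusion that the described study does not produce.

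What is at stake is interpretation. If Group A does better than Group B, a reader planning a school program could take 45 minutes, three times a week, at the stated heart-rate range as the amount shown to be best or necessary. The comparison would give no information on whether less, more, gentler or harder activity would do as well.

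**Working it through.** **1. Levels assigned (Table 1, Intervention).**

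| Feature | Group A | Group B | Levels compared |
|---|---|---|---|
| Session length | 45 min | none | one against none |
| Frequency | 3 days/week | none | one against none |
| Program length | 12 weeks | none | one against none |
| Heart-rate range | about 120–180 beats/min | none | one against none |

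Offered time is 45 × 3 = 135 minutes a week, and 135 × 12 = 1,620 minutes = 27 hours in all, the same for every Group A child. The age-based targets follow the child's age; they are not alternative intensities set up for comparison.

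**2. What the article's power calculation covers.** Inputs from Data analysis: effect size 0.8, alpha 0.05 one-tailed, power 0.8. Normal approximation per group: 2 × (1.645 + 0.842)² / 0.8² = 2 × 6.18 / 0.64 = 19.3, rounded up to 20. The exact t-test solution is 20.03, rounded up to 21, so 42 in total. This reproduces the stated 21 per group and 42 in total. It is a calculation for program versus no program; no contrast in intensity or duration was powered.

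**3. Stated analyses against the promise.**
- Descriptive statistics would summarise heart rate, but do not relate it to scores.
- The t-tests compare Group A with Group B.
- The mixed model is given to account for baseline differences; no intensity or exposure term is named.
- Within-group changes show whether a group's mean moved, not whether children with more or harder activity moved further.

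**4. What an added Group A analysis could detect.** Assumptions, not in the article: two-sided 0.05, 80% power, a simple correlation between one exposure measure and academic change, and all 50 planned Group A children analysed.

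Fisher z: smallest detectable value = (1.96 + 0.84) / √(50 − 3) = 2.80 / 6.856 = 0.409; tanh(0.409) gives r of about 0.39. If only 40 are analysed: 2.80 / √37 = 0.460, giving r of about 0.43.

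Power with 50 children is Φ(atanh(r) × √47 − 1.96):

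| True r | Power |
|---|---|
| 0.1 | about 10% |
| 0.2 | about 28% |
| 0.3 | about 56% |

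Splitting Group A into 25 lower-intensity and 25 higher-intensity children would detect only a standardised difference of about 0.81. If the difference were 0.5, power would be 41%.

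**The case against.** Several points can fairly be made in the article's defence.

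- **Insight is a modest word, and dose-finding is not a formal objective.** The stated objective is the effect of the program on academic performance, behavior, emotions and health measures. This limits the damage: no objective and no sample size depends on the claim. But the object of the insight is the ideal amount necessary for an academic gain, which is a dose-response statement however gently introduced.
- **Exposure will vary and is measured.** With freely chosen activity and age-based targets, achieved intensity will differ between children. A reader might infer that the heart-rate recordings are never used, or are the only relevant data. The article supports neither: descriptive statistics are promised for all data, which covers heart rate, and the PAQ-C measures activity in both groups. Using the PAQ-C in all 100 planned children, the same formula gives 2.80 / √97 = 0.284, or r of about 0.28. That route is observational too, and pooling the groups mixes amount of activity with group membership.
- **A full protocol or SAP may contain an exposure-response analysis.** A reader might also count its absence, or the absence of attendance and adherence reporting, as a defect. It is not one here, because a journal article commonly leaves such detail to those documents. What does not depend on them is the conflict between the promised conclusion and the design: an added regression cannot create a second assigned duration or intensity.

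**Conclusion.** The point holds as a mismatch between a stated conclusion and the stated design. One assigned duration and one broad intensity range are compared with no program, so the study can at most show whether this program differs from none. It cannot rank durations or intensities. Variation in achieved intensity comes from the children's own behaviour and may be confounded, for example by fitness and motivation.

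It would go too far to say that the data can tell us nothing about received activity. An exploratory analysis is possible, but it would be observational and low-powered: r of about 0.39 detectable with 50 Group A children and about 0.43 with 40, under the assumptions given in the working. These figures describe the optional analysis; the main point rests on the design alone. The planned comparison of Group A with Group B and its sample size are not affected.

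**What to change.** Delete the claim about ideal intensity and duration in both the Abstract and the closing Discussion, or restrict it to the effect of this single program as offered.

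If a statement about intensity is kept, base it on a prespecified exploratory analysis in Group A. Relate change in academic score, adjusted for baseline score, to mean recorded heart rate as the measure of intensity. Examine minutes in range or attendance separately, because minutes in range mixes intensity, time and attendance and cannot stand for intensity alone. Label the result observational and low-powered, and do not describe any level as ideal or necessary.

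The required change is one sentence in two places. The optional analysis uses data that the article already says will be collected. The downside is a narrower claim.
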